To evaluate the effects on brain transmission and the underlying mechanisms of this modulation, specific intracortical circuits will be investigated using transcranial magnetic stimulation (TMS), which depends on various neurotransmitters. Over the years, numerous TMS protocols have been developed to obtain neurophysiological parameter information for investigating both the pathogenesis and progression of certain neurodegenerative diseases. Cholinergic brain activity will be assessed using the short-latency afferent inhibition (SAI) protocol (Tokimura et al., 2000). Additionally, electroencephalographic modifications and biological parameters will be analyzed.

**OBJECTIVES:** The aim of this study is to evaluate clinical and biological response markers to home-based transcranial alternating current stimulation (tACS) supervised via telemedicine by investigators in patients with Alzheimer's disease (AD).

**PROCEDURES:** Patients followed at the Neurological Clinic, ASST Spedali Civili di Brescia, and the Neurology Unit, G. Giglio Institute Foundation, Cefalù (PA), with an AD diagnosis based on current clinical criteria, will be enrolled and randomized into two groups:

The first group (group 1) will undergo stimulation protocol using tACS (real), while the second group (group 2) will undergo placebo treatment (sham) (double-blind phase), with a real:placebo ratio of 1:1. Both group 1 and group 2 will then follow an open-label phase with real tACS stimulation. The treatment will be administered during the first week in the hospital, and thereafter, it will be provided at home with supervision from one of the experimenters via telemedicine.

During the first week, the patient and caregiver will receive training at the hospital, where staff will explain how to position and use the device. On the first day, staff will show the patient and caregiver the procedures. On the following days, they will let the caregiver manage the device and will provide support during treatment administration in order to enable the caregiver to manage the device independently at home. During this period, the study's medical staff will assess compliance with the correct procedures and, therefore, the caregiver's ability to manage the device independently. At the end of the training procedure, the investigator will assess the

[figure not shown][figure not shown][figure not shown]

CLINICA NEUROLOGICA - UNIVERSITA' DEGLI STUDI DI BRESCIA  

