#### PLACEBO GROUP - GROUP 2:

In the placebo group, the setup will be the same as for real stimulation; however, the electrical current will be automatically interrupted 60 seconds after the start of each stimulation, so that the placebo stimulation is indistinguishable from the real one. The same tests and assessments used during real stimulation will be applied.

After two months of treatment, all patients will undergo an open-label phase with real tACS for an additional 2 months, following the same protocol as group 1, and a subsequent follow-up 2 months after the end of treatment. In addition, two further follow-up visits will be carried out at three months and 12 months, where only clinical evaluation will be performed.

Analysis of Biological and Genetic Markers: the following biological and genetic biomarkers of response to tACS will be analyzed:

-ApoE and BDNF Genotyping: Genomic DNA will be extracted from whole peripheral blood using the Maxwell® 16 Blood DNA Purification Kit with the Maxwell® 16 Instrument (both Promega). The regions containing both APOE polymorphisms rs429358 and rs7412, as well as BDNF rs6265, will be amplified through polymerase chain reaction (PCR) using GoTaq® Hot Start Polymerase (Promega) or Optimase® Polymerase (ADS Biotech). PCR products will be purified with 0.5 mL Amicon® Ultra centrifugal filters (Merck Millipore). Sequencing will be performed using the AB Prism Big Dye Terminator Sequencing 3.1 kit (Life Technologies), following the manufacturer's instructions. The sequences will then be purified using ID MicroSEQ™ sequencing cleanup cartridges (Life Technologies) and loaded onto a 3500 Genetic Analyzer (Life Technologies). All sequences will be analyzed using Chromas software (Technelysium Pty Ltd).

- Plasma Marker Quantification (NfL, pTau, Abeta40/42, and GFAP): plasma NfL will be measured using the commercial NF-light® assay (Quanterix, Lexington, MA) according to the manufacturer's instructions. p-Tau, Abeta40/42, and GFAP will be measured using the Simoa platform.

-Analysis of extracellular vesicles (EVs) from blood with analysis of neurodegeneration/inflammation markers (miRNomic profile). EVs will be isolated from plasma/serum using a commercial kit (Total Exosomes Isolation Kit,

[figure not shown][figure not shown][figure not shown]

CLINICA NEUROLOGICA - UNIVERSITA' DEGLI STUDI DI BRESCIA  
UO Neurologia 2 - AZIENDA SOCIO SANITARIA TERRITORIALE degli SPEDALI CIVILI DI BRESCIA  
Direttore: [name]

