#### **INCLUSION CRITERIA for the caregiver:**

- Signed Informed Consent Form
- Age  $> 18$  years
- Compliance in participating in training on device usage
- Mini-Mental State Examination (MMSE)  $> 27/30$

[figure not shown][figure not shown][figure not shown]

CLINICA NEUROLOGICA - UNIVERSITA' DEGLI STUDI DI BRESCIA  
UO Neurologia 2 - AZIENDA SOCIO SANITARIA TERRITORIALE degli SPEDALI CIVILI DI BRESCIA  
Direttore: [name]

213

214 **EARLY WITHDRAWAL CRITERIA from the study:**

- 215 - Difficulty in managing the device, measured by the procedure failure rate, as  
216 indicated by the reliability code generated by the device after two training  
217 sessions at the center.

218

219 **STUDY DESIGN:** it is a monocentric, interventional, non-pharmacological,  
220 placebo-controlled, randomized, double-blind clinical study, as neither the patients  
221 nor those administering the evaluation tests will be aware of the type of treatment  
222 provided, real tACS or placebo, followed by an open-label phase. The stimulation  
223 equipment will be pre-programmed (real stimulation or placebo) by another operator  
224 who will not administer the stimulation itself or the tests, thus ensuring the  
225 experimental double-blind. Both the operator administering the treatment and the  
226 operator performing the evaluations will be unaware of the type of stimulation  
227 administered.

228 At baseline (T0), at the end of the double-blind phase (T1, 8 weeks), at the end of the  
229 open-label phase (T2, 16 weeks), and after further follow-up (T3, 24 weeks), each  
230 subject will undergo clinical and neuropsychological evaluation, TMS, EEG, and  
231 blood sampling for the assessment of biological markers such as NfL, pTau,  
232 Abeta40/42, and GFAP. The biological samples will then be sent to the Molecular  
233 Markers Laboratory at the IRCCS Istituto Centro San Giovanni di Dio  
234 Fatebenefratelli in Brescia for analysis of biological markers on extracellular vesicles  
235 from plasma or serum.

236 A subgroup of patients will undergo brain MRI (resting state) at baseline (T0) and at  
237 the end of the double-blind phase (T1, 8 weeks).

238 Each subject will then undergo two further follow-up visits with clinical evaluation at  
239 36 weeks (T4) and 72 weeks (T5) from T0.

240

241 **OBJECTIVES:**

- 242 - Primary objectives: evaluate the tolerability and safety of transcranial alternating  

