## END POINTS:

- Primary objectives: it is expected that tACS will be well tolerated (% of compliance >50%) and safe (absence of major adverse events) in the studied population. The effectiveness of the treatment will be evaluated on dedicated tests.

- Secondary objectives: the effectiveness of the treatment on imaging parameters will be evaluated. The effectiveness of the treatment on neurophysiological parameters and plasma neurodegeneration/amyloidosis will be evaluated.

- Exploratory objectives: it is expected that certain biological factors at baseline (e.g., ApoE genotype) may modulate the degree of response to tACS and thus predict the degree of clinical response.

**STATISTICAL PLAN:** as an experimental design, we will use a linear mixed-effects model (LME) with TIME (T0, T1, T2, T3) as a within-subject factor and TREATMENT (sham/real vs real/real) as between-subject factors, considering the subject modeled as a random intercept effect.

We performed a power analysis with G\*Power to estimate the sample size, based on some previously published studies (Benussi et al., *Brain Stimul* 2021; Dhaynaut et al., *J Alzheimers Dis* 2022; Zhou et al., *J Neurol Neurosurg Psychiatry* 2021), using methodologies similar to those applied in the study in question. The effect size  $f(V)$  was calculated using the direct method. Taking into account from the aforementioned studies an effect size equal to a partial  $\eta^2$  of 0.080, corresponding to an effect size  $f(V)$  of 0.295, and considering  $\alpha = 0.05$  and power  $(1-\beta) = 0.90$ , the expected sample size is 34 total subjects. Taking into account a possible attrition rate of 50%, appropriate for long-term studies in patients with Alzheimer's disease, who may have poor tolerability to the device, the final required sample size amounts to 50 total subjects (25 per group).

Correlation analyses (Pearson correlations corrected for multiple comparisons with False Discovery Rate) will be used to evaluate the correlations between biological parameters (plasma neurodegeneration markers) and clinical response. For dichotomous measures (ApoE and BDNF genotype), Fisher's exact test will be used.

**ETHICAL CONSIDERATIONS (RISK-BENEFIT):** tACS is a non-invasive, low-cost, and easy-to-implement technique that is gaining increasing popularity and an expanding range of potential therapeutic applications.

[figure not shown][figure not shown][figure not shown]

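### The protocol does not separate stopping stimulation from leaving the study, so the week-8 real-versus-sham contrast may rest mainly on patients who could use and tolerate the device

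*Protocol*

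**What the plan says.** The sample-size paragraph (Protocol, Statistical plan, under End points) finds that "the expected sample size is 34 total subjects". It raises this to 50, 25 per group, for a "possible attrition rate of 50%, appropriate for long-term studies in patients with Alzheimer's disease, who may have poor tolerability to the device". No time point, split by cause or split by arm is given for the 50%.

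Two rules take a patient off the device:

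- Under Procedures, a patient whose caregiver is still not independent after the second training week is excluded from the study.
- Under Early withdrawal criteria, difficulty in managing the device, shown by the reliability code after two training sessions, leads to withdrawal from the study.

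Study design schedules the clinical and neuropsychological evaluation for each subject at T0, T1 (8 weeks), T2 and T3. T1 closes the double-blind phase, and both groups then receive real stimulation.

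The efficacy analysis is a linear mixed model over T0 to T3, "considering the subject modeled as a random intercept effect". In the sham arm, "the electrical current will be automatically interrupted 60 seconds after the start of each stimulation".

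**The concern.** Stopping the device and leaving the study are different events. A patient who no longer uses the device can still take the CDR-SB, ADAS-Cog13, FNAT and ADCS-ADL at week 8. The protocol treats the two events as one where it sets rules (exclusion and withdrawal are from the study) and where it sizes the trial (poor device tolerability is counted as attrition). It nowhere describes a patient who is off stimulation and still in follow-up.

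T1 is the last assessment at which the arms differ by real versus sham. If patients who stop have no T1 score, the contrast is driven by those who continued, and it may not describe the 50 patients randomised. Tolerability is itself a primary objective, so these patients matter to the question asked. Whether their scores are collected is a protocol matter, because no later analysis plan can recover data that were never taken.

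**Working it through.** **The plan's own figures.** Partial η² = 0.080 gives f = √(0.080/0.920) = 0.295, as stated. The number of measurements and their correlation are not given. Assume two measurements (m = 2) and r = 0.5, with noncentrality f²·N·m/(1−r) on 1 and N−2 degrees of freedom. Power is then 0.907 at N = 33 and 0.915 at N = 34, so 34 reproduces. The step to 50 does not: 34/(1−0.5) = 68, and 50 × 0.5 leaves 25. That is a separate point, and nothing below rests on it. What matters here is that the 50% is used as a loss of analysable patients.

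**Exposure before T1.** Eight weeks of five sessions is 40 sessions. Real stimulation is 40 × 60 = 2,400 minutes of current, and sham is 40 × 1 = 40 minutes. The ethics section lists tingling, burning or pain sensations, headache and nausea. Stopping that differs by arm is therefore possible, but the documents do not show it.

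**How the model treats missing T1.** A patient with T0 only adds almost nothing to the T1 contrast. The model relies on missing at random and in effect gives that patient the mean change of patients in the same arm who have T1.

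**Illustrative size.** From the plan: 25 per arm. Assumed:

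- T0–T1 correlation 0.7, so the SD of change is √(2 × 0.3) = 0.775.
- Benefit b in patients who continue and none in those who stop.
- Stoppers' course worse by g, with each arm's untreated mean held at zero.
- No T1 score for stoppers.

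The value b = 0.46 SD is also what the plan's f gives if it is read as the group effect on T0–T1 change: 2 × 0.295 × 0.775 = 0.457.

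Continuers in an arm with stopping share p average g·p above the arm mean. So:

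- estimate without stoppers' T1 = b + g(p_real − p_sham)
- effect over all randomised = b(1 − p_real)

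| Stopping real/sham | b | g | Estimate | All randomised |
|---|---|---|---|---|
| 25%/25% | 0 | 0 or 0.5 | 0 | 0 |
| 25%/25% | 0.46 | 0 | 0.46 | 0.345 |
| 50%/50% | 0.46 | 0 | 0.46 | 0.23 |
| 25%/10% | 0 | 0.5 | 0.075 | 0 |
| 40%/10% | 0 | 0.5 | 0.15 | 0 |
| 40%/10% | 0.46 | 0.5 | 0.61 | 0.276 |

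**False-positive rate with no true effect.**

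- At 40%/10%, 15 and 22.5 patients remain. SE = 0.775 × √(1/15 + 1/22.5) = 0.258, and 0.15/0.258 = 0.58. Two-sided rejection is about 9% by normal approximation; a simulation of 4,000 trials gave 8.8%.
- At 25%/10%, 18.75 and 22.5 remain, SE = 0.242, and the rate is about 6%.

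**If 80% of stoppers attend T1 (40%/10%, g = 0.5).**

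- Real: (0.60 × 0.20 − 0.32 × 0.30)/0.92 = 0.026.
- Sham: (0.90 × 0.05 − 0.08 × 0.45)/0.98 = 0.009.
- The spurious difference falls from 0.15 to about 0.017 (simulation 0.015, rejection 5.0%).
- With b = 0.46 the estimate becomes 0.017 + 0.60 × 0.46/0.92 = 0.317, against 0.276 over all randomised.

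**The case against.** The case against a stronger claim is good, and most of it stands.

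- **No T1 score for stoppers.** A reader might infer that the plan denies these patients a week-8 score. No passage says so, and Study design plans T1 for each subject. The two listed rules concern operating the device, not how stimulation feels, so no rule removes a patient for intolerance. The inclusion criteria also ask for a caregiver who has already completed training, so some training exclusions may precede randomisation, although Procedures places training in the first treatment week.
- **Half the patients lost to intolerance by week 8.** A reader might take the 50% as 25 of 50 patients on this path. It is an all-cause allowance described for long-term studies, in a protocol with visits to week 72. Loss by T1 may be far smaller.
- **Analysis restricted to tolerators.** The mixed model has no such restriction. It keeps every observed score, including T1 from a patient who stopped and attended.
- **Analysis sets and imputation.** These may be in a statistical analysis plan that is not shown, so their absence is not raised here.
- **Assumed sizes.** Zero benefit in every stopper, a 0.5 SD worse course and 40%/10% stopping are not in the documents. Sham is meant to be indistinguishable from real, and side effects are described as minimal.

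None of this supplies the missing provision. Planning T1 for each subject does not settle whether someone withdrawn from the study returns for it, and the text does not say which statement governs.

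**Conclusion.** The point holds as a gap in data collection. The protocol ends study participation for device failure, counts poor device tolerability within attrition, and does not say that patients who stop or are withdrawn are still assessed at T1. The only placebo-controlled contrast is therefore at risk of resting mainly on patients who could use and tolerate the device.

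The size and even the presence of bias are unknown. With no true effect, equal stopping in both arms with the same stopper shortfall produces none. A spurious benefit needs both more stopping on real and a worse course in those who stop: about 0.075 SD at 25%/10% and 0.15 SD at 40%/10%, each with a 0.5 SD shortfall. The effect over all randomised patients falls below that in continuers only if stoppers get little benefit. The documents do not support saying that the trial will overstate the effect.

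**What to change.** In Study design, next to the Early withdrawal criteria, state that any randomised patient who stops or is withdrawn from stimulation, for any reason, is still asked to attend T1 and the later scheduled visits for the four primary tests, unless consent to assessment is withdrawn. This changes no rule on when stimulation ends.

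In the Statistical plan, state that all randomised patients are analysed in their allocated arm using those scores. Replace the single 50% with two allowances, one for stopping stimulation and one for a missing T1 score.

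The cost is wording, plus attendance by patients who have stopped at visits that the protocol already schedules. The estimated effect, and the power for it, will be somewhat smaller if stoppers gain little:

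- In the simulation with b = 0.46 SD and 25% stopping in each arm, power is 0.43 without stoppers' scores and 0.35 with 80% of them assessed.
- Under the assumptions that reproduce 34, with 20% stopping and no benefit in them, it is 0.953 in the 40 who continue and 0.905 in all 50.

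### 50 enrolled with 50% attrition leaves 25 patients, not the 34 required for 90% power

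*Protocol*

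**What the plan says.** The sample-size justification is one paragraph of the Protocol, in STATISTICAL PLAN under END POINTS. It starts from a partial η² of 0.080, "corresponding to an effect size $f(V)$ of 0.295", with α of 0.05 and power of 0.90, and reports that "the expected sample size is 34 total subjects". The next sentence opens "Taking into account a possible attrition rate of 50" per cent, gives long follow-up and possible poor tolerability of the device as the reasons, and ends: "the final required sample size amounts to 50 total subjects (25 per group".

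Allocation is set in PROCEDURES ("with a real:placebo ratio of 1:1"). The planned analysis is a "linear mixed-effects model (LME) with TIME (T0, T1, T2, T3) as a within-subject factor". The Protocol gives no second attrition rate, no rule for replacing lost patients and no other enrolment figure.

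**The concern.** An attrition rate is the share of enrolled patients who are lost. The number to enrol is therefore the number needed at the end divided by the share retained. Going from 34 to 50 raises the completers by about half, which is a different and smaller correction. The gap between the two widens as attrition rises and is large at 50%.

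This paragraph is the trial's only sample-size justification. An ethics committee or later reader would take from it that 50 patients protect 90% power against the loss of half of them. If the trial found no effect, the result would be read as coming from a 90%-powered study when the plan's own attrition assumption says otherwise.

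**Working it through.** **Inputs, all from STATISTICAL PLAN:** 34 subjects from the power analysis; attrition 0.50; final total 50 (25 per group); partial η² 0.080; α 0.05; power 0.90.

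**1. Attrition step.** This uses only the 34, the 50% and the 50.

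- Correct inflation, n/(1 − d): 34/(1 − 0.50) = 68, or 34 per group.
- Adding the percentage instead, n × (1 + d): 34 × 1.50 = 51. The stated 50 is within one patient of this and 18 short of 68.
- Patients left from 50 enrolled: 50 × (1 − 0.50) = 25, which is 34 − 25 = 9 too few.
- Largest attrition at which 50 enrolled still leaves 34: 1 − 34/50 = 0.32.

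**2. Reproducing the plan's 34.** The effect-size conversion is right: f = √(0.08/0.92) = 0.295. The Protocol names G*Power but gives neither the number of measurements (m) nor the correlation between them (ρ), so both are assumptions here. For a within-between interaction with k = 2 groups, the noncentral F has

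- λ = f² × N × m/(1 − ρ)
- df1 = (k − 1)(m − 1), df2 = (N − k)(m − 1)

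With m = 2 and ρ = 0.5:

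- N = 34: λ = 0.08696 × 34 × 2/0.5 = 11.83, df 1 and 32, power 0.915. This is the smallest even total that reaches 0.90, so the stated 34 is reproduced.
- N = 25: λ = 0.08696 × 25 × 2/0.5 = 8.70, df 1 and 23, power 0.806.

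**3. Range over the unstated settings.** For m of 2, 3 and 4, ρ was varied in steps of 0.01 and every setting that returns 34 was kept.

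| m | ρ returning N = 34 | Power at 34 | Power at 25 |
|---|---|---|---|
| 2 | 0.48–0.50 | 0.905–0.915 | 0.791–0.806 |
| 3 | 0.34–0.37 | 0.904–0.917 | 0.783–0.803 |
| 4 | 0.20–0.24 | 0.901–0.916 | 0.774–0.797 |

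Power with 25 patients is therefore 0.77 to 0.81. The type II error goes from the planned 0.10 to between 1 − 0.806 = 0.19 and 1 − 0.774 = 0.23, about double.

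**The case against.** The strongest counter-argument is that the planned mixed model uses partial data. A patient lost after T1 still supplies the randomised double-blind comparison, and the Protocol does not say whether the 50% runs to week 8, 24 or 72. If most losses come late, the real drop in power is smaller than the table shows. That stands as a limit on the size of the loss. It does not rescue the paragraph, which counts whole subjects, inflates for attrition and makes no partial-data argument. Some of the expected losses may also be early: the text cites poor tolerability of the device, and PROCEDURES and EARLY WITHDRAWAL CRITERIA remove patients whose caregiver cannot manage it after training.

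The power figures rest on unstated inputs. This is correct, and they are offered only as a range conditional on settings that return 34. Other effect-size conventions in the same software do not return 34 at all (56 to 168 for the interaction under the settings tried), so they cannot be used to follow the plan's reasoning. The contradiction in step 1 needs none of this.

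How the 50 arose is an inference, since 34 × 1.5 is 51 and not 50. That is fair. If a 50% uplift was what the authors meant, then calling it an attrition rate is wrong, and the true allowance is about 32%.

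The consequence is a misreported design figure, not a biased analysis. That is also fair, but the figure is printed in the Protocol, and a statistical analysis plan would not repair it.

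**Conclusion.** The concern holds. The 34 subjects, the 50% attrition and the 50 enrolled are mutually inconsistent. At 50% attrition, 50 enrolled leaves 25, nine short, and reaching 34 needs 68. Enrolling 50 is adequate only if attrition is at most 32%. This conclusion rests on the stated figures alone.

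The fall in power from 0.90 to about 0.77–0.81 is an estimate. It assumes a two-group repeated-measures interaction test with settings chosen to return the plan's own 34, and that lost patients contribute nothing. The sentence is wrong as written and must be corrected.

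**What to change.** Rewrite the attrition sentence so that its three figures agree. Two versions keep enrolment at 50:

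- **(a) Restate the attrition.** Say that 50 enrolled (25 per group) yields 34 evaluable patients if attrition is no more than 32%, counted up to T1, the 8-week end of the double-blind phase, rather than over long-term follow-up. The 32% is only back-calculated from 50, so the sponsor must justify it separately.
- **(b) Keep 50% attrition.** Say that 50 enrolled yields 25 evaluable patients, and give the power at 25 (about 0.77 to 0.81 on the settings above). Name the number of measurements and the correlation used in G*Power.

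Either costs one sentence in the Protocol and no extra patients, but the stated tolerable attrition or the stated power becomes less favourable. If the sponsor wants to keep both 50% attrition and 90% power, the total must be 68 (34 per group), which is 18 more patients.

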#### TREATMENT GROUP - GROUP 1:

The treatment group will undergo tACS sessions (real at 3 mA) applied at the cortical level for 60 minutes/day for 8 weeks, 5 days a week (Monday to Friday). The effects of tACS will be assessed both before and after stimulation, specifically evaluating cognitive performance using dedicated tests (i.e., CDR-SB, ADAS-Cog13, FNAT, ADCS-ADL), neurophysiological parameters (SAI using TMS and brain rhythms using electroencephalography [EEG]), and biological parameters (NfL, pTau, Abeta40/42, and GFAP). In a subgroup, effects on brain magnetic resonance imaging (resting state) will also be evaluated. A 6cc blood sample will also be taken to

[figure not shown][figure not shown][figure not shown]

CLINICA NEUROLOGICA - UNIVERSITA' DEGLI STUDI DI BRESCIA

UO Neurologia 2 - AZIENDA SOCIO SANITARIA TERRITORIALE degli SPEDALI CIVILI DI BRESCIA

Direttore: [name]

determine the ApoE and BDNF genotype, subject to the signing of an informed consent form, in order to evaluate any markers of clinical response.

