243 current stimulation (tACS) and its effectiveness on dedicated tests (CDR-SB, ADAS-  
244 Cog13, FNAT, ADCS-ADL).  
245 - Secondary objectives: evaluate the effectiveness of tACS on neurophysiological  
246 imaging parameters, markers of neurodegeneration/plasma amyloidosis.

[figure not shown][figure not shown][figure not shown]

CLINICA NEUROLOGICA - UNIVERSITA' DEGLI STUDI DI BRESCIA

UO Neurologia 2 - AZIENDA SOCIO SANITARIA TERRITORIALE degli SPEDALI CIVILI DI BRESCIA

Direttore: [name]

- Exploratory objectives: evaluate clinical and biological markers at baseline (cognitive reserve index questionnaire, ApoE genotype, BDNF) in response to tACS.

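### Fisher's exact test, the only analysis stated for ApoE and BDNF genotype, cannot show whether genotype modifies the effect of tACS

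*Protocol*

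**What the plan says.** The exploratory objective in the Protocol (OBJECTIVES) concerns baseline markers ("cognitive reserve index questionnaire, ApoE genotype, BDNF) in response to tACS"). The matching entry under END POINTS expects that such factors, with ApoE genotype as the example, "may modulate the degree of response to tACS and thus predict the degree of clinical response".

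The STATISTICAL PLAN covers genotype in one sentence, which begins "For dichotomous measures (ApoE and BDNF genotype" and goes on only to name Fisher's exact test. It names no second variable, arm, time point, responder definition or carrier grouping. The sentence before it describes Pearson correlations with FDR correction, which "will be used to evaluate the correlations between biological parameters (plasma neurodegeneration markers) and clinical response".

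The main model is a linear mixed model with TIME and "TREATMENT (sham/real vs real/real) as between-subject factors, considering the subject modeled as a random intercept effect". It has no genotype term. The clinical outcomes are scale scores ("i.e., CDR-SB, ADAS-Cog13, FNAT, ADCS-ADL"). Allocation is 1:1, and after T1 (8 weeks) both groups receive real stimulation.

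**The concern.** Whether a factor modulates the degree of response to a treatment is a question about effect modification of a graded outcome. To answer it, the real-versus-sham difference has to be compared between genotype groups. Fisher's exact test of genotype by response makes no such comparison. It asks whether genotype and outcome are associated, either over all patients or within one arm.

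A genotype that only marks faster or slower decline, whatever the treatment, can therefore be taken for a predictor of response to tACS. A genuine modifier whose effects run in opposite directions in the two arms can be missed. The trial has one sham-controlled window, T0 to T1, in which the question can be put properly, and the stated test does not use its contrast.

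**Working it through.** **No protocol figure to reproduce.** The protocol gives no power, sample size or effect size for the genotype analysis.

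**Step 1: what each test targets.** Let T = 1 for real and 0 for sham, G = 1 for carriers, and let the continuous outcome be

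Y = α + βT + γG + δTG + ε.

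Here γ is the prognostic effect of genotype and δ is the modification of the tACS effect. The mean difference in Y between carriers and non-carriers is:

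- sham arm: γ
- real arm: γ + δ
- both arms pooled at 1:1: ½γ + ½(γ + δ) = γ + δ/2

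Fisher's test on a categorised Y looks for the pooled or the real-arm quantity. The objective concerns δ, which is the real-arm difference minus the sham-arm difference. Three cases:

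| Case | γ | δ | Pooled γ + δ/2 | Real arm γ + δ | Interaction δ |
|---|---|---|---|---|---|
| Purely prognostic | 0.8 | 0 | 0.8 | 0.8 | 0 |
| Pure modifier | 0 | 1.0 | 0.5 | 1.0 | 1.0 |
| Opposite effects by arm | -0.5 | 1.0 | 0 | 0.5 | 1.0 |

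In the first case Fisher's test has something to find and the interaction does not. In the third the pooled table has almost nothing to find although the modification is large. This part needs no assumed effect size.

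**Step 2: how large the problem could be.** Inputs from the protocol: 1:1 allocation, N = 50 (25 per group) or 34 (before attrition), α = 0.05. Assumptions not in the protocol: two-sided testing, ε normal with SD 1, β = 2 × 0.295 = 0.59 SD, 50% carriers, response cut at the pooled median, and the values of γ and δ. Each setting has 4,000 simulated trials, so the Monte Carlo standard error is √(0.05 × 0.95/4000) = 0.3 percentage points near 5% and √(0.5 × 0.5/4000) = 0.8 near 50%. The table gives the percentage of trials significant; a dash means not computed.

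| Setting | N | Fisher, pooled | Fisher, real arm | Interaction |
|---|---|---|---|---|
| No genotype effect | 50 | 3.1 | 3.8 | 5.3 |
| Prognostic 0.2 SD | 50 | 5.0 | 5.2 | - |
| Prognostic 0.3 SD | 50 | 9.4 | 6.5 | - |
| Prognostic 0.5 SD | 50 | 21 | 12 | 5.0 |
| Prognostic +0.8 SD | 50 | 46 | 26 | 5.6 |
| Prognostic -0.8 SD | 50 | 50 | 27 | 4.6 |
| Prognostic 0.3 SD | 34 | 5.2 | 5.2 | - |
| Prognostic 0.5 SD | 34 | 12.6 | 9.1 | - |
| Prognostic 0.8 SD | 34 | 29.0 | 17.2 | 5.2 |
| Modifier 1 SD | 50 | 14.5 | 31.9 | 39.6 |
| Modifier 1 SD | 34 | 9.7 | 21.4 | 27.8 |
| Opposite effects (-0.5, +0.5) | 50 | 3.5 | 10.6 | 40.7 |
| Opposite effects (-0.5, +0.5) | 34 | 2.1 | 6.4 | 26.4 |

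A repeat run at N = 50 gave 21-47% pooled and 14-25% in the real arm for 0.5 to 0.8 SD, and about 4-8% for 0.2 to 0.3 SD. With 30% carriers and 0.8 SD, Fisher's test is significant in 36.6% (pooled) and 17.6% (real arm) at N = 50, and in 21.0% and 9.9% at N = 34.

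**The case against.** **The target of Fisher's test is inferred.** This is true: the sentence names no second variable. Clinical response is the natural reading, because the sentence follows the one on correlation with response and the exploratory endpoint concerns response. The other reading, genotype frequencies compared between arms, would remove the complaints about categorised scores and the missing treatment contrast. It would also leave the exploratory objective with no genotype analysis.

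**Details belong in a statistical analysis plan.** Responder cut-offs, carrier coding and arm handling may properly be left there, and their absence is not held against the protocol. But the protocol itself fixes the test, and no cut-off or coding gives a genotype-by-response table a treatment contrast.

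**The size depends on the inputs chosen.** This stands. Fisher's test is conservative with no genotype effect (about 3-4% at N = 50). It reaches only about 4-9% for a prognostic effect of 0.2 to 0.3 SD, and inflation is smaller at N = 34.

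**The interaction gains little power.** This also stands against the real-arm test: 39.6% versus 31.9% at N = 50, and 27.8% versus 21.4% at N = 34, for a 1 SD modifier. The gain is in what a significant result means.

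**Further inferences the protocol does not support.** A reader might object that ApoE and BDNF genotypes are not dichotomous. Calling them so implies a carrier grouping, which is a usual and acceptable coding. A reader might also conclude that the Pearson correlations should go. The plasma markers are measured at T0 to T3, serve the secondary objective, and are not named in the exploratory one. The correlation sentence can be read as relating marker change to clinical change, which is a different and legitimate analysis. Finally, Fisher's test extends beyond 2 × 2 tables, so it needs categories but not necessarily two.

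**Conclusion.** The concern holds for the genotype analysis. The stated test does not match the stated question on either reading: as genotype by response it cannot tell a modifier from a prognostic marker, and as genotype by arm it does not address response.

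The mismatch itself rests on no assumption. Its practical size does. With 25 per arm, half carriers and a median split, a purely prognostic effect of 0.5 to 0.8 SD gives significant Fisher results in about 21-50% of trials pooled and 12-27% in the real arm, against about 5% for the interaction. At 0.2 to 0.3 SD the figure is about 4-9%.

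A reader might infer that the plan will produce false predictors of response. The documents do not support that, since they give no prognostic effect for either genotype. False predictors could arise if that effect is large. The objective is exploratory, and the primary analysis is untouched. Severity is minor to moderate.

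**What to change.** Replace Fisher's test for ApoE and BDNF with a genotype (carrier yes/no) × TREATMENT term in a model of the continuous T0-T1 change on each clinical scale. The equivalent in the mixed model is the genotype × TREATMENT × TIME contrast at T1. State the carrier grouping in advance. Report each interaction estimate with its 95% confidence interval. Include these tests in the FDR correction, which the plan now states only for the correlations; two genotypes and four scales make 2 × 4 = 8 tests. Label the analysis exploratory.

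Keep the planned Pearson correlations, and add a sentence that they are not evidence that a marker modulates the tACS effect.

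The cost is wording only, since genotype and outcomes are already to be collected in both arms. The drawback is low power: roughly 25-40% for a 1 SD modifier at N = 34 to 50. A non-significant interaction will say little, and any finding remains hypothesis-generating.
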